The community-based model is predominantly run by a Cambodian nongovernmental organization called MoPoTsyo that operates Peer Educator Networks with 4 main key services for patients with T2D or HT or both. These services include (1) self-management training through peer educator visits, (2) laboratory tests, (3) physician consultations, and (4) low-cost medicines delivered through a revolving drug fund program to the members in the network in 8 out of 24 provinces across the country. By 2019, 255 peer educators have been trained to serve over 40,000 patients [20]. In this community-based model, peer educators, who are patients with T2D or HT or both themselves, have been trained by MoPoTsyo to be educators and counselors on lifestyle change. Peer educators also assist registered patients in the networks to have access to professional medical consultations at the public referral hospitals with which they have partnership agreements [20].

These 3 care models are implemented in isolation with relatively little interaction between each other. There have been few empirical studies on their performance. The question arises as to what extent the 3 care models have performed in providing care to people with T2D or HT or both in Cambodia. Care models that are integrated in terms of shared information and resource coordination have shown to be effective and efficient in many contexts [21]; however, implementation and scale-up of effective care models for T2D and HT remain limited, especially in LMICs. How well different models perform in contributing to good health outcomes is also not well documented. The outcomes of chronic care are difficult to measure, as such care does not have a clear end point, but requires comprehensive illness management along a continuum of care, from detection and diagnosis for initiating treatment and follow-up to successful management of the illness. This complexity requires a comprehensive framework of measurement to assess the performance of care for T2D and HT.

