Inspired by noticeable successes in providing the continuum of care to people living with HIV in Cambodia [22], we adapted the HIV test-treat-retain cascade of care [23] in this study protocol to assess the continuum of care for patients living with T2D or HT or both. This method documents how many patients are lost to follow-up between the stages of testing and diagnosis, linkage with and retention in care, and adherence to treatment and control of health conditions. The cascade-of-care approach outlines the aforementioned sequential steps in long-term care. Recently, this approach has been applied to T2D and HT by pooling secondary data from cross-sectional studies of nationally representative surveys in LMICs [24,25]. This was used to produce cascades of care as an approach to assess the performance of health systems to meet the continuum of care for patients living with T2D or HT or both. Two studies, one in the United States and the other in South Africa, developed and field tested the cascade of care for T2D and HT [26,27]. Their analysis was mainly based on extracted secondary data from broader nationally representative surveys, not specifically designed for this purpose.

Given that Cambodia implements T2D and HT services through 3 different care models, we propose the cascade-of-care approach to assess the performance of these care models along the continuum of care. We will do so using primary data collection. This study protocol aims to serve as a tool to generate the cascades of care for T2D and HT for the 3 care models using the primary data of a population-based survey. The specific aims are as follows:

To generate the cascades of care for T2D for (1) hospital-based care, (2) health center–based care (WHO PEN), (3) community-based care (Peer Educator Network), and (4) coexistence of 1, 2, and 3;To generate the cascades of care for HT for (1) hospital-based care, (2) health center–based care (WHO PEN), (3) community-based care (Peer Educator Network), and (4) coexistence of 1, 2, and 3;To compare the cascades of care for T2D between the care models 1-4;To compare the cascades of care for HT between the care models 1-4.

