### Statistical Analysis Plan

For the analysis plan, 6 cascade bars, as explained in Tables 2 and 3, will be used to generate the cascades of care for T2D and HT, respectively. A fixed denominator approach will be followed as it enables readers to see the leakages between stages of the continuum of care [39]. The denominator is the total number of eligible individuals aged 40 and above having T2D (for the T2D cascade of care) and HT (for the HT cascade of care). We will produce the cascade of care for T2D and HT for the selected ODs hosting different existing care models. These cascades of care—in essence, a series of bar charts—will subsequently be translated into cumulative probabilities. The bivariate analysis will be used to identify potential factors associated with the outcome variables—prevalence, testing, diagnosis, in care, in treatment, and under control bars. At the initial stage, the chi-square test will be used to determine the association between explanatory variables and outcome variables. The explanatory variables will include participants’ age, sex, marital status, educational level, household wealth quintile, health care utilization, and care model setting. Variables with statistically significant level (*P*<.2) will be included in a multiple logistic regression model. In addition to the aforementioned variables, BMI, lifestyle, knowledge of T2D and HT, self-management, and social support will be included in the multiple logistic regression model for the outcome variables—in care, in treatment, and under control bars [24,25]. In the multiple logistic regression model, the backward elimination method will be used. The process will start with all the identified explanatory variables. Then, variables with the highest *P* value will be eliminated from the model one by one at a time. The process will be repeated until all the variables in the model are statistically significant with a cut-off point of *P* value <.05. This knowledge will allow us to identify which characteristics stimulate the probability of not reaching the next step in the cascade of care, thereby identifying patient groups not adequately reached.

**Table 2 table2:** Defined groups of participants for each bar of the cascade of care for T2D^a^.

Bars of the cascade of care for T2D	Definitions	Questions extracted for analysis

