1. Prevalence of the target population living with T2D	Participants having biochemical measurement of FBG^b^ (capillary plasma value) ≥126 mg/dl (7 mmol/L) and HbA_1c_^c^ level ≥6.5% [24,40,41]	Measurement of FBG Measurement of HbA_1c_
		Have you ever been told by a doctor or other health worker that you have T2D?
	or Participants reporting use of drugs for T2D, irrespective of their biomarker values	
2. Number of the target population with T2D ever tested for T2D	Classified patients with T2D having had FBG tested in the last 3 years	Have you ever had your blood glucose tested in the last 3 years?
3. Number of those tested ever diagnosed for T2D	Tested patients with T2D reporting ever being told by a doctor or other health worker as having T2D	Have you ever been told by a doctor or other health worker that you have T2D?
4. Number of those diagnosed in care	Diagnosed patients with T2D reporting getting treatment/care for their conditions at least once in the past 12 months	Did you get treatment/care for your T2D condition in the past 12 months?
5. Number of those in care receiving treatment	In-care patients with T2D reporting using drugs for T2D or insulin in the past 2 weeks or in-care patients with T2D reporting following advice to lose weight, stop smoking, do physical exercise, and be on special prescribed diet	Are you currently receiving any of the following treatment/advice for your T2D condition prescribed by a doctor or health care worker? Insulin or drugs (medication) that you have taken in the past 2 weeks Are you currently receiving any of the following treatment/advice for your T2D condition prescribed by a doctor or health care worker? Special prescribed diet and advice to lose weight and advice to stop smoking and advice to start or do more physical exercise
6. Number of those receiving treatment being under control	In-treatment patients with T2D having HbA_1c_ level <8% [24]	Measurement of HbA_1c_ for the known T2D

^a^T2D: type 2 diabetes.

^b^FBG: fasting blood glucose.

^c^HbA_1c_: glycated hemoglobin A_1c_.

**Table 3 table3:** Defined groups of participants for each bar of the cascade of care for HT^a^.

Bars of the cascade of care for HT	Definitions	Questions extracted for analysis
1. Prevalence of the target population living with HT	Participants having systolic blood pressure ≥140 mmHg or diastolic blood pressure ≥90 mmHg [12] or	Measurement of blood pressure (mean of the second and third readings)

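### The only adjusted comparison of care models conditions on things the models deliver, and it can drop care model altogether

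*Protocol article*

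**What the plan says.** The third specific aim in the Introduction is "To compare the cascades of care for T2D between the care models 1-4", and the fourth is the same for hypertension.

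The Statistical Analysis Plan section first produces cascades for the selected operational districts (ODs) and turns them into cumulative probabilities. Chi-square tests then relate explanatory variables to six outcomes: prevalence, testing, diagnosis, in care, in treatment and under control. The explanatory variables are age, sex, marital status, education, "household wealth quintile, health care utilization, and care model setting". The entry rule is: "Variables with statistically significant level (*P*<.2) will be included in a multiple logistic regression model".

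A second group is then added: "BMI, lifestyle, knowledge of T2D and HT, self-management, and social support will be included in the multiple logistic regression model", but only "for the outcome variables—in care, in treatment, and under control bars". Elimination goes on "until all the variables in the model are statistically significant with a cut-off point of *P* value <.05". No term is named as one that must stay in. The section gives the purpose of the regression as finding characteristics linked to leakage from the cascade and patient groups that are poorly reached.

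The Introduction describes what the care models do. The first listed service of the peer educator network is "self-management training through peer educator visits". Its educators also counsel on lifestyle and help members reach medical consultations. Health centers give health education and counselling on healthy behavior.

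In Table 2, bar 4 (in care) is defined as "Diagnosed patients with T2D reporting getting treatment/care for their conditions at least once in the past 12 months". Bar 5 (in treatment) can be met by recent medication, or by following advice on weight, smoking, exercise and diet. Table 3 has the same structure for hypertension, with salt in place of diet.

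**The concern.** A comparison of care models asks how outcomes differ between settings, by whatever route the model works. A covariate that the model itself changes lies on that route. Once it is held fixed, the care-model coefficient describes at most the remaining, direct part. Utilization, lifestyle, knowledge and self-management are all candidates for such a covariate on the protocol's own description.

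Backward elimination adds a second problem. If these variables carry much of the effect, care model may no longer reach P<.05 and is removed. The final model would then suggest that the setting does not matter, although the setting may be what changed the variables that stayed in.

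This matters because no other adjusted comparison is described. A reader looking for an answer to the third and fourth aims that allows for age, sex, education and wealth would have only this coefficient.

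**Working it through.** **1. Which covariates are part of the models' work.** Setting the Introduction beside the covariate list:

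- Self-management: a named service of the peer network. Enters bars 4 to 6.
- Lifestyle: counselled by peer educators and by health centers. Enters bars 4 to 6.
- Knowledge: addressed by health education at health centers. Enters bars 4 to 6.
- Health care utilization: peer educators help members reach consultations. Can enter all six outcomes if P<.2.
- Social support and BMI: no passage says that the models act through them. Enter bars 4 to 6.

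The first four are downstream of care model on the article's own account. For the last two this would be inference.

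**2. Possible overlap with the outcomes.** Bar 4 is itself a report of having used care for the condition. One route into bar 5 is following lifestyle advice. Utilization and lifestyle could therefore partly repeat these outcomes. Whether they do depends on Multimedia Appendix 6, which is not shown.

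**3. Number of patients.** The plan gives no figure for mediation, so its sample-size figures serve only to set the scale. The formula reproduces: 1.96² × 0.1 × 0.9 × 1.5 × 1.2 / (0.24 × 4.6 × 0.01²) = 5637.1, against the stated 5637. The adopted sample is 5 × 44 × 24 = 5280. At 10% prevalence this gives 5280 × 0.1 / 5 = 105.6, or about 106 diabetes patients per OD. With the 5072 recruited it is about 101.

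**4. Illustration with assumed inputs.** Two ODs of 106 patients were simulated, 1000 runs per scenario, with one binary mediator and baseline log-odds of −1.0. The assumptions are a mediator prevalence of 30% in one OD and 50% or 60% in the other, and a mediator-outcome odds ratio (OR) of 3, 6 or 10. None of these comes from the documents. Clustering and weights were ignored.

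The smallest case by hand: the outcome risk is 1/(1 + e^1.0) = 0.269 without the mediator and, at OR 3, 0.525 with it.
- OD A: 0.7 × 0.269 + 0.3 × 0.525 = 0.346.
- OD B: 0.5 × 0.269 + 0.5 × 0.525 = 0.397.
- Total OR = (0.397/0.603) / (0.346/0.654) = 1.25, while the OR within each mediator level is 1.

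Results over all scenarios:

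| | Effect wholly through the mediator | Added direct OR of 1.5 |
|---|---|---|
| Total care-model OR | 1.25 to 1.87 | 1.82 to 2.52 |
| Median OR with mediator in the model | 1.00 to 1.02 | 1.48 to 1.57 |
| Runs in which care model is eliminated | 94% to 96% | 70% to 77% |
| Runs in which the unadjusted test gives P<.05 | 12% to 64% | 55% to 90% |

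The first column is built to give an adjusted OR of 1, so it shows the mechanism and is not an estimate. The second shows that care model can usually be dropped even when a direct effect remains.

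**The case against.** The strongest reply is that this regression is not offered as the care-model comparison. Its stated purpose is to find factors linked to leakage, and knowledge, self-management and lifestyle are fair candidates for that. The cascades by OD, the cumulative probabilities and the chi-square test for care model setting condition on none of them. This stands as a limit on the harm: total differences remain visible. It does not remove the point, because those analyses are unadjusted. The five ODs were chosen purposively, in different provinces, and may differ in age, education and wealth.

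A second reply is that BMI, social support and even lifestyle may be case-mix differences in a cross-sectional survey, so that leaving them out risks confounding. For BMI and social support this stands.

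A reader might go further and infer three things that the documents do not support:

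- That real differences vanish. Only the mediated part is lost, and an adjusted OR of 1.00 follows only if full mediation is assumed.
- That the community-based model loses most. That model also provides laboratory tests, physician consultations and low-cost medicines. Laboratory tests and medicines are not listed as covariates, and nothing ranks the loss across models.
- That utilization and lifestyle restate bars 4 and 5 and will dominate those models. Their definitions are not shown. Utilization could mean general use of services, while bar 4 is specific to the condition. Bar 5 can be met by medication alone.

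**Conclusion.** The point holds as a fault of structure. The only adjusted analysis that bears on the third and fourth aims gives at most a direct effect of care model, and its elimination rule can remove the term. Utilization is at issue for all six outcomes if it passes the P<.2 screen. Lifestyle, knowledge and self-management are at issue for in care, in treatment and under control only.

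The size of the loss cannot be known from the documents, and the simulated figures rest entirely on assumed mediator prevalences and odds ratios. The conclusion itself needs only the protocol's description of what the models deliver and its covariate list.

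**What to change.** For the third and fourth aims, add one set of models with care model setting kept in whatever its P value, adjusted only for age, sex, marital status, education and wealth quintile. BMI and social support may be added in a sensitivity analysis, since they could be confounders.

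Report the fuller model, with utilization, lifestyle, knowledge, self-management, social support and BMI, separately as an exploratory factor analysis. State that its care-model coefficient is not to be read as a total effect. Where the appendix definition of utilization or lifestyle overlaps the bar 4 or bar 5 questions, leave that predictor out of the model for that outcome.

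The cost is some wording and one extra set of models. No new data are needed, and the article reports that analysis was still pending. One limit remains under either covariate set: with one OD per care-model setting, the coefficient cannot be separated from other differences between the ODs, and the report should say so.

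### Care model setting, the exposure of aims 3 and 4, is open to P-value deletion, so the only adjusted care-model comparison the plan states can vanish for any bar

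*Protocol article*

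**What the plan says.** The specific aims at the end of the Introduction include "To compare the cascades of care for T2D between the care models 1-4" and "To compare the cascades of care for HT between the care models 1-4". Table 1 maps each of the five ODs to a care model setting. The ODs were chosen purposively and sampled in equal numbers so that each model has enough participants.

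The Statistical Analysis Plan section describes two layers of analysis.

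- **Descriptive.** A cascade with a fixed denominator is produced for each disease in each selected OD and then turned into cumulative probabilities.
- **Regression.** The explanatory variables end with "household wealth quintile, health care utilization, and care model setting", so care model stands in the same list as age, sex and education. At the outset "the chi-square test will be used to determine the association between explanatory variables and outcome variables". Those with P<.2 "will be included in a multiple logistic regression model". Then: "In the multiple logistic regression model, the backward elimination method will be used". As to scope, "The process will start with all the identified explanatory variables". The variable with the highest P value is removed, one at a time, and "The process will be repeated until all the variables in the model are statistically significant" at P<.05.

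No sentence exempts care model setting from either step, and no other adjusted comparison of care models is described.

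**The concern.** In a study whose aims name a comparison, the compared factor is normally held in the model and its estimate is reported with an interval, whatever its P value. Here it competes with the covariates for a place. Three consequences follow.

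1. If care model is eliminated for a bar, that bar has no adjusted care-model estimate and no interval. Imprecise data and truly similar models then produce the same blank.
2. If it is retained, the estimate is reported because it was significant. Such estimates are on average too large, and the nominal interval takes no account of the selection.
3. Elimination is run separately for each outcome, so the covariates left beside care model can differ between bars and between diseases. Adjusted differences then cannot be followed along the cascade.

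The adjusted comparison matters because the ODs lie in five provinces and were not randomised to a care model. Unadjusted bars cannot separate care model from age, education or wealth.

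**Working it through.** **Step 1. The plan's own figures.** The formula under Sampling and Sample Size gives 1.96² × 0.1 × 0.9 × 1.5 × 1.2 / (0.24 × 4.6 × 0.01²) = 5637.1, against 5637 stated. The fixed design gives 24 × 44 × 5 = 5280, as stated. Both reproduce.

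**Step 2. Cases per OD.** Recruited: 5072 (Results). Per OD: 5072/5 = 1014.4. At the plan's 10% diabetes prevalence this is about 101 cases per OD. The plan's design effect of 1.5 reduces it to 101/1.5 ≈ 67 effective cases. The fixed denominator makes this the base for the diabetes bars after the first; the prevalence bar has all participants as its base, so the figures below do not apply to it.

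**Step 3. Approximation.** One unadjusted test of five OD categories (4 df) stands in for the stepwise procedure. With n cases per OD, design effect d, OD proportions pᵢ and mean p̄, the noncentrality is λ = (n/d) × Σ(pᵢ − p̄)² / [p̄(1 − p̄)]. The chance of failing is the noncentral chi-square probability below 9.488 (P<.05) or 5.989 (P<.2). The documents give no bar values, so every pᵢ is an assumption.

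**Step 4. Diabetes, four ODs at 50%, one at 60%.** p̄ = 0.52; Σ = 4 × 0.02² + 0.08² = 0.008; λ = 101 × 0.008/0.2496 = 3.24.

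**Step 5. Diabetes, graded 40/45/50/55/60%.** p̄ = 0.50; Σ = 0.025; λ = 101 × 0.025/0.25 = 10.1.

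**Step 6. Hypertension, assumed 30% prevalence, 50/60 pattern.** n = 1014.4 × 0.30 ≈ 304; λ = 304 × 0.008/0.2496 = 9.74.

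| Scenario | λ (d = 1) | Fails P<.05, d = 1 | Fails P<.05, d = 1.5 |
|---|---|---|---|
| Diabetes, one OD at 60%, four at 50% | 3.24 | 74% | 82% |
| Diabetes, one OD at 65%, four at 50% | 7.30 | 44% | 61% |
| Diabetes, graded 40–60% | 10.1 | 28% | 48% |
| Hypertension at 30%, one OD at 60%, four at 50% | 9.74 | 30% | about 50% |
| Hypertension at 30%, one OD at 65%, four at 50% | 21.97 | 2% | 12% |

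In the first scenario care model fails even the P<.2 screen in 47% of studies (57% at d = 1.5).

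**Step 7. Exaggeration when kept.** In a simulation of the first scenario without clustering, the true advantage of the fifth OD is 10 points. Among studies in which the test reached P<.05, the mean estimated advantage was just under 16 points.

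**The case against.** A reader might infer that the plan contains no other comparison of care models, or that aims 3 and 4 are answered only where P<.05. The text does not support either. The cascades are produced for every OD whatever the P values, and each OD is mapped to a care model. The chi-square test of care model against each bar is run before any elimination. The aims speak of comparing cascades and do not ask for adjusted odds ratios. What can be lost is the adjusted estimate, and the point is limited to that.

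The regression also has its own stated purpose: to find the characteristics of patients who do not reach the next step. For an exploratory search of that kind, backward elimination is a common choice. This stands as a description of the model, but care model setting is explicitly placed in it and no other model serves the aims. Nor is this a detail left to a fuller plan, because the thresholds, order and stopping point are all written down.

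The P<.2 screen may not govern every bar. For the in-care, in-treatment and under-control outcomes, the wording can be read as entering the listed variables directly. Elimination at P<.05 applies in either case.

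The magnitude depends on the assumed pattern. A graded spread, a larger gap or the more common disease gives much lower failure rates than 74%, as the table shows. Low power for differences in diabetes control is a separate matter that the plan discloses when it says a sufficient sample would need five times the budget. Keeping care model in the model would not narrow its interval. It would ensure that the estimate and its imprecision are reported.

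That readers would take elimination as proof of no difference is a prediction about readers, and the point does not rest on it.

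**Conclusion.** The point holds for the adjusted comparison and should be fixed. By the written rule, care model setting must survive backward elimination at P<.05 for every bar, and a P<.2 screen for at least the earlier bars. The adjusted care-model estimate can therefore be deleted, or kept only when significant, with an adjustment set that varies between bars. The descriptive comparison by OD and the bivariate test are unaffected.

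This conclusion follows from the rule and needs no assumed rates. The rates show only how often the rule could bite: from 28% to 82% for diabetes, and from 2% to about 50% for hypertension at an assumed 30% prevalence, across the patterns examined. These figures assume equal ODs, five OD categories, 10% diabetes prevalence and one unadjusted test in place of the stepwise procedure.

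Adjustment would deal only with measured covariates. It would not remove other differences between purposively chosen districts.

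**What to change.** State in the Statistical Analysis Plan section that the care-model (OD) indicator stays in the model for every bar and both diseases, whatever its P value. Prespecify one adjustment set, the same across bars, drawn from the sociodemographic variables already collected. Which of these belong in it is for the investigators to decide and justify; the documents do not settle the list. Report the adjusted care-model estimates with 95% CIs for every bar.

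If the search for characteristics of patients not reached is still wanted, keep P-value selection for a separate model labelled exploratory.

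The cost is a change of wording with no new data, and the Results section says analysis is still pending. The downside is that some non-significant terms remain in the models.

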^a^OD: operational district.

^b^NCD: noncommunicable disease.

^c^In the WHO PEN implementation arrangement, the referral hospital in the OD supports the health centers in providing the secondary care.

^d^WHO PEN: World Health Organization Package of Essential Noncommunicable Disease Interventions.

^e^The Peer Educator Network arranges a medical consultation for their registered patients once a week at the referral hospital in the OD.

This population-based survey includes 2 questionnaires (Multimedia Appendices 1 and 2). One questionnaire is directed at household heads and inquires about the household’s socioeconomic status, member characteristics, general health of the household members, and their access to health care and health-related expenditure. The other questionnaire is for eligible adults (ie, adults aged ≥40) of the selected households and inquires about their sociodemographic information, health status and comorbidity, quality of life, health care utilization, social support, behavioral measurements, and knowledge of T2D and HT for known patients with T2D or HT or both in particular. Known patients with T2D or HT or both are also asked about their medical adherence and decision-making power over diet.

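### The regressions take cumulative, fixed-denominator bars as outcomes but are read as failure at the next step, so an early-step difference will tend to show up at later bars

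*Protocol article*

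**What the plan says.** All of this is in the Statistical Analysis Plan section of the protocol article.

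- **Denominator.** "A fixed denominator approach will be followed as it enables readers to see the leakages between stages of the continuum of care". It is then defined: "The denominator is the total number of eligible individuals aged 40 and above having T2D", with the equivalent for HT.
- **Scale.** The cascades "will subsequently be translated into cumulative probabilities".
- **Regression outcomes.** The bivariate tests, and the logistic models that follow them, have as outcomes the "prevalence, testing, diagnosis, in care, in treatment, and under control bars". Care model setting is one of the explanatory variables.
- **Interpretation.** The models are meant to "identify which characteristics stimulate the probability of not reaching the next step in the cascade of care".
- **Nesting.** Tables 2 and 3 build each bar from the one before. Bar 3 for T2D counts "Tested patients with T2D reporting ever being told by a doctor or other health worker as having T2D" and bar 4 counts "Diagnosed patients with T2D reporting getting treatment/care for their conditions at least once in the past 12 months". Bars 5 and 6 continue in the same way, and the HT table has the same structure.

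The article nowhere limits a regression to people who reached the preceding bar.

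**The concern.** Because the bars are nested, a bar over a fixed denominator is a product of step probabilities. A logistic model on the treatment bar, for example, contrasts people in treatment with everyone else who has the disease: never tested, tested but undiagnosed, diagnosed but not in care, and in care but untreated. Its odds ratio reflects all the steps up to that bar. Failure at the next step concerns only those who stood at the step before.

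The study aims to locate leakages and to compare care models. If cumulative odds ratios are read as step-specific ones, a factor that acts only on testing can be reported as a barrier to care, treatment or control, and attention is drawn to the wrong stage.

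**Working it through.** The plan states no odds ratio or step probability, so there is no figure of its own to reproduce on this point. Its planned sample does reproduce (24 households × 44 villages × 5 districts = 5280). It is used below only for the expected number of T2D cases at the plan's 10% prevalence: 0.10 × 5280 = 528.

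**Formulas.** Let q₂ be the chance of being tested given disease, q₃ diagnosed given tested, q₄ in care given diagnosed, q₅ treated given in care, and q₆ controlled given treated. The fixed-denominator bar k is B_k = q₂ × … × q_k. For two groups a and b, the cumulative odds ratio is [B_k,a/(1 − B_k,a)] / [B_k,b/(1 − B_k,b)]. The step-specific odds ratio uses q_k in place of B_k.

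**Illustration 1 (assumed values, not in the documents).** Testing is 75% in group a and 50% in group b; q₃ = q₄ = q₅ = 0.70 in both.

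| Bar | Group a | Group b | Cumulative OR | Step-specific OR |
|---|---|---|---|---|
| Tested | 0.75 | 0.50 | 3.00 | 3.00 |
| Diagnosed | 0.525 | 0.35 | 2.05 | 1.00 |
| In care | 0.3675 | 0.245 | 1.79 | 1.00 |
| In treatment | 0.2573 | 0.1715 | 1.67 | 1.00 |

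Last row: (0.2573/0.7427) / (0.1715/0.8285) = 1.67.

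**Illustration 2 (assumed values, not in the documents).** Testing is 80% against 60%; in both groups diagnosed given tested is 75%, in care given diagnosed 80%, treated given in care 90%, and controlled given treated 50%. The cumulative odds ratios from testing to control are 2.67, 1.83, 1.64, 1.59 and 1.43. The step-specific ones are 2.67 and then 1.00 at each of the four later steps.

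**Range.** Three testing contrasts (80/60, 80/50 and 90/70%) were crossed with three sets of later-step probabilities that were equal between groups. The spurious odds ratios at later bars ran from 1.33 to 3.14.

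**How often this would be called significant.** Illustration 2 was simulated 4000 times with 528 T2D cases in two equal groups, using unweighted two-proportion tests at two-sided 0.05.

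| Later bar, no true step difference | Fixed denominator | Among those at the previous bar |
|---|---|---|
| Diagnosed | 94% | about 5% |
| In care | 80% | about 5% |
| In treatment | 73% | about 5% |
| Under control | 35% | about 5% |

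The simulation ignores the sampling weights, the plan's design effect of 1.5 and covariates, so actual detection rates would be lower. The direction does not depend on these.

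**The case against.** **The regression denominator is inferred.** The fixed denominator is introduced to let readers see leakages in what are essentially bar charts, and the regression sentences name no analysis population. It cannot govern every model, because prevalence is a listed outcome and would be 100% among cases. Row labels in Tables 2 and 3 can also be read conditionally. This stands as a caution: the text is not an explicit instruction to fit the wrong model. But the only stated denominator is the fixed one, and the named outcomes are the bars it defines. The row labels say who is counted in each bar, not over whom. A conditional intention would still need to be stated.

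**A condensed article leaves detail to the full plan.** True, but nothing is said to be missing. The article itself states a denominator, outcomes and an interpretation, and these do not fit together.

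**The charts protect the care-model comparison.** Separate cascades by operational district show the drop between adjacent bars, whatever the regressions do. This limits the harm for care models described in the charts. It does not correct the reading of the regression coefficients.

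**The cumulative model has a legitimate use.** It does show which groups are poorly reached overall. That is a reason to label it correctly if it is kept.

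**A stronger reading to avoid.** The article describes the individual questionnaire as covering "knowledge of T2D and HT for known patients with T2D or HT or both in particular", and knowledge is added as a predictor from the in-care bar onward. A reader might infer that undiagnosed people have no knowledge value and drop out of those models. The wording does not establish that knowledge is asked only of known patients, and the questionnaire is not shown. If it were so, it would work against the main concern: in Illustration 1 the treatment bar among the diagnosed is 0.70 × 0.70 = 49% in both groups, an odds ratio of 1.00.

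**Conclusion.** The mismatch holds. On the plain reading, the plan models the cumulative chance of reaching each bar among all with the disease and interprets it as failure at the next step. A characteristic or care model that differs only early in the cascade will then tend to show an association at later bars. In the assumed examples the later odds ratios are about 1.3 to 3.1 where the step-specific value is 1.00.

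This rests on the fixed denominator applying to the regressions for bars 2 to 6 (prevalence necessarily uses all participants) and on step probabilities that the documents do not give. A reader might go further and infer that an early barrier must be reported at every later step. That is not supported. The carry-over weakens down the cascade, may miss P<.05 at the control bar and so be removed by backward elimination, and can be offset by an opposite later effect. The point is one of analysis population and interpretation; the fixed-denominator charts themselves are sound.

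**What to change.** Keep the fixed denominator for the bar charts. State the analysis population of each regression, and fit the step-specific models among those who reached the previous bar:

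- tested, among all with T2D (or HT);
- diagnosed, among the tested;
- in care, among the diagnosed;
- treated, among those in care;
- controlled, among the treated.

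Report any fixed-denominator regression that is kept as the probability of reaching that bar among all with the disease. Rewording alone would remove the contradiction, but only the conditional models answer the stated question.

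No new data are needed, and the article reports that analysis was still pending. The cost is fewer people and wider intervals at later steps, and comparison groups selected by having passed the earlier ones. The T2D control model is the tightest. With 528 cases and the treated shares of Illustration 1 it would have roughly 528 × 0.1715 = 91 to 528 × 0.2573 = 136 people, against the 12 explanatory variables or domains the section names (seven general, five added for the last three bars). The number of candidates there may need limiting.
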